Figure 4: Brain diffusion measures were sampled in the infant brains at term equivalent. demonstrating decreased Anterior Limb of Internal Capsule diffusivity (p<0.05); increased left Frontal Lobe anisotropy (p<0.05) and trend to decreased diffusivity (p=0.07); and decreased left centrum Semiovale diffusivity (p<0.05). These changes are consistent with a more mature white matter in the infants whose mothers received pomegranate juice.

Figure 5: Brain Metrics representing brain growth demonstrated that infants who had pomegranate exposure in their mothers had larger biparietal diameters (3a) and smaller interhemispheric distances (5) and interopercular distances (4a, 4b) representing better brain growth and less extra-axial space than infants whose mothers received apple juice.

[figure not shown]

The present study seeks to investigate the impact of maternal dietary supplementation with pomegranate juice or its extract on the placenta and newborn brain development and function. This study will uniquely undertake concurrent examination of placentas and infant brain outcomes to examine the mechanism of potential benefit in IUGR.

**Hypothesis:** Maternal consumption of pomegranate juice in the last trimester of pregnancy will result in improved newborn brain development and placental function compared to infants with mothers who consume a placebo.

**Specific Aim:** To study the impact maternal polyphenol rich PJ administration has on placental function; brain injury and development (by MRI) at term and neurodevelopmental outcome at 18-24 months in infants with IUGR.

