**Interpretation of results:** We expect pomegranate-exposed placentas to show less evidence of oxidative stress, more trophoblast mass, and less evidence of fibrin deposition microscopically and by immunoblotting. We expect less apoptosis and more evidence of trophoblast differentiation in the pomegranate group. We will consider any differences in the light of biological significance, also, as small statistically significant differences may prove relevant to the infant outcomes. Although highly unlikely based on the known effects of pomegranate, we will note any adverse effect from pomegranate extract, such as enhanced oxidative stress, increased fibrin deposition as a sign of injury, or diminished terminal villi lower than control.

Infant Neurobehavior: All infants will have a formal Dubowitz neurologic exam and an attention evaluation using the Hammersmith Neonatal Neurological Examination Optimality score at term equivalent (38-41 weeks post menstrual age). Furthermore, formal neurodevelopmental follow up will take place at 18-24 months of age.

MRI Evaluation

If clinically stable, MRI will be undertaken without sedation at term equivalent (38-41 weeks CGA). The MRI evaluation will include the following analysis:

a) Systematic qualitative scoring of the nature and extent of brain injury

b) Diffusion analysis of the cortical, white matter and posterior limb of the internal capsule to generate apparent diffusion coefficients (ADC).

c) Spectroscopy over the left basal ganglia

d) Brain metrics measuring the length of certain regions of the brain and comparing to standardized values

e) Assessment of MRI developmental indices such as volume and surface folding (SBM)

| **Measure** | **White Matter** | **Gray Matter** |
| --- | --- | --- |
| Qualitative | WM lesion score/  ventriculomegaly | Cortical and DNGM injury score |
| Metrics | Frontal lobe volume, | Intrahemispheric volume loss, ventricular size |
| Volumetry | Total myelinated and unmyelinated WM volumes | Total cortical gray matter, DNGM and CSF volumes  Hippocampal volume |
| Diffusion | Two measures (ADC, RA) each measured on 8 pairs of volume –derived lesions | Two measures (ADC, RA) on:   1. 6 pairs of surface-based regions 2. 8 pairs of volume-derived regions |
| MRS | N/A | Lactate and NAA measures over the L basal ganglia |
| SBM | NA | Four measures (cortical surface area, average sulcal depth, integrating folding index, and percentage buried cortex) |

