**Biostatistical Analyses**

**General methods:**

The statistical methods employed in this study will be complex and will be undertaken with the assistance of [name], biostatistician in the Department of Pediatrics. Clinical data such as maternal risk factors, birth weight, placental weight, gestation, need for resuscitation in the DR, etc. will be collected for both the intervention and the control group during the perinatal course.

The primary outcomes will be either a) brain injury or b) delayed development at 18-24 months. The relationship of placental function and measures to these outcomes will be explored to understand the mechanism of neuroprotection.

Brain injury will be defined as any of the following (see Table 3):

- Moderate to severe injury by qualitative scoring of WMI or GMI
- Diffusion scores (ADC, FA) > 2 SD from normal term infants
- Spectroscopy showing elevated lactate and decreased NAA (hypoxic injury) over the L basal ganglia
- Bottom 25% percentile in brain metrics, volumetric indices, or measures of surface based morphology (SBM) compared to the general healthy population.

Delayed development will be classified as:

- BSID III (MDI or PDI) > 2 SD (< 70) below the normal population

* MRS- MR Spectroscopy; SBM- Surface-based morphology

Table 2. Definition of CNS Injury by US/ MRI

| **Modality** | **Technique** | **Measures** | **Likelihood of injury** | **Definition of**  **Injury** |
| --- | --- | --- | --- | --- |
| Ultrasound |  | Grade IVH | Low | Grade 2-4 |
| MRI | Qualitative | WMI, GMI | Low | Mod-Severe injury |
|  | Diffusion/Spect | ADC, FA  Lactate, NAA | High  Low | > 2 SD above term  Lactate ↑, ↓NAA |
|  | Metrics | Intraparietal diameter, extra cranial space | High | Bottom 25% of the population |
|  | Volumetric | Total volume,  Cerebral gray matter volume, | High | Bottom 25% of the population |
|  | SBM | Cortical surface area, average sucal depth, integrated folding index | High | Bottom 25% of the population |

Continuous variables will be compared using a student t-test when they are parametric and Mann-Whitney test when they are nonparametric. Categorical variables (such as moderate or severe white matter injury) will be compared using either a chi-squared (for parametric) or a Kruskal-Wallis test for nonparametric one way analysis of variance. This is a pilot study where the results will assist in the planning of a larger randomized controlled trial.

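### The brain-injury primary outcome counts some favourable MRI results as injury and misses the adverse ones, which dilutes the treatment difference

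*Protocol*

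**What the plan says.** In the Protocol, Biostatistical Analyses, General methods, the primary endpoint reads "The primary outcomes will be either a) brain injury or b) delayed development at 18-24 months". The first of these is a composite: "Brain injury will be defined as any of the following".

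Two components matter here.

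- **Diffusion.** The text bullet has "Diffusion scores (ADC, FA) > 2 SD from normal term infants", with no direction. In Table 2 the cell shared by ADC and FA has "> 2 SD above term".
- **Metrics.** Table 2 lists "Intraparietal diameter, extra cranial space" and gives both the same rule, the lowest 25% of the population. The text bullet applies the same lowest-quarter rule to metrics, volumes and surface morphology.

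The pilot results in the Background show which direction the investigators regard as good. The Figure 4 legend reports decreased diffusivity and "increased left Frontal Lobe anisotropy (p<0.05", and takes both as signs of greater white-matter maturity. The Figure 5 legend reports larger biparietal diameters and smaller interhemispheric and interopercular distances, "representing better brain growth and less extra-axial space than infants whose mothers received apple juice".

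The anisotropy index also changes name. The MRI Evaluation table has "Two measures (ADC, RA", while Outcome measures and General methods use FA.

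**The concern.** By the protocol's own reading of its pilot, ADC and FA improve in opposite directions, and so do head diameter and extra-axial space. One shared tail cannot be the adverse tail for both members of either pair. The Table 2 rules suit ADC and diameter and are reversed for FA and the space measure.

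Because one positive component is enough, a reversed component can label a better-developed infant as injured, and an infant with low FA or an enlarged space is not picked up by that component. If pomegranate juice works as hypothesised, the reversed components move against it and offset part of the fall in the others. General methods says that the results will help plan a larger trial, so an attenuated event-rate difference would carry into that design too.

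**Working it through.** The protocol gives no injury rate, power or effect size, so there is no figure of its own to reproduce.

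**Step 1: direction, from the documents**

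| Measure | Favourable direction (Figures 4 and 5) | Counted as injury in Table 2 | Adverse tail scored? |
|---|---|---|---|
| ADC | lower | high | yes |
| FA | higher | high | no |
| Diameter | larger | lowest 25% | yes |
| Extra cranial (extra-axial) space | smaller | lowest 25% | no |

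Read as two-sided, the bullet adds low FA but still counts high FA, and also low ADC, as injury.

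**Step 2: the two reversed components**

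Assumptions, not in the documents: each measure is normal and standardised to healthy term infants; controls are b SD worse than that norm; the benefit is d = 0.5 SD. Let h = −b for controls and h = d − b for pomegranate.

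- FA above +2 SD: 1 − Φ(2 − h)
- Space in the lowest 25%: Φ(−0.674 + h)

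| Control deficit b | FA, control → pomegranate | Space, control → pomegranate |
|---|---|---|
| 0 | 1 − Φ(2.0) = 2.3% → 1 − Φ(1.5) = 6.7% | 25.0% → Φ(−0.174) = 43.1% |
| 0.5 | 1 − Φ(2.5) = 0.6% → 2.3% | Φ(−1.174) = 12.0% → 25.0% |
| 1.0 | 1 − Φ(3.0) = 0.1% → 0.6% | Φ(−1.674) = 4.7% → 12.0% |

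Both rise with benefit at every baseline. With the tails turned round, both fall: at b = 0.5, FA goes from 6.7% to 2.3% and space from 43.1% to 25.0%.

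Under a two-sided reading of the bullet, FA goes from 4.6% to 7.3% at b = 0, but falls from 7.3% to 4.6% at b = 0.5 and from 16.0% to 7.3% at b = 1.

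**Step 3: the composite**

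I simulated 400,000 infants per arm in each scenario with nine markers: ADC, FA, diameter, space, two volumes and three surface measures. Qualitative injury, spectroscopy and ultrasound were left out. The benefit was 0.5 SD on every marker, with a common correlation of 0, 0.3, 0.6 or 0.9. Entries are the change in the composite rate (pomegranate minus control, percentage points), Table 2 as written / tails corrected.

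| b | corr. 0 | corr. 0.3 | corr. 0.6 | corr. 0.9 |
|---|---|---|---|---|
| 0 | −11.7 / −27.4 | −6.6 / −25.4 | −3.6 / −22.6 | +0.3 / −18.0 |
| 0.5 | −10.0 / −11.0 | −9.4 / −17.5 | −8.4 / −20.2 | −7.2 / −20.2 |
| 1.0 | −2.6 / −1.6 | −6.0 / −7.5 | −8.3 / −13.2 | −10.7 / −17.8 |

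The composite as written falls in 11 of 12 scenarios; in the other it is flat (64.0% to 64.3%). The fall is smaller than with corrected tails in 11 of 12. The exception is b = 1 with correlation 0, where nearly every infant is positive under either rule (control rates 99.8% and 99.9%).

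**Step 4: power at correlation 0.3**

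With 80 women allocated 1:1, n = 40 per arm, and two-sided 0.05 (assumed), power = Φ((|difference| − 1.96·SE₀)/SE₁), where SE₀ is the pooled and SE₁ the unpooled standard error.

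| b | As written: rates, power | Corrected: rates, power |
|---|---|---|
| 0 | 82.1% → 75.5%, 11% | 72.5% → 47.1%, 65% |
| 0.5 | 91.6% → 82.1%, 24% | 90.0% → 72.5%, 52% |
| 1.0 | 97.5% → 91.6%, 22% | 97.7% → 90.1%, 29% |

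These powers assume that every infant is scanned; in the pilot, 30 infants were scanned from 41 randomised mothers.

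**The case against.** A reader might infer that a true benefit would raise the overall injury rate in the pomegranate arm. The documents do not support that. Most components point the right way, and the composite fell in 11 of 12 scenarios. A rise of any size appeared only when the composite was cut down to diffusion and metrics with controls at the term norm (48.5% to 54.6% at correlation 0.3).

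The FA part can also be called small. The Background describes growth-restricted preterm infants with reduced brain volumes and abnormal diffusion, so an impaired baseline is the more likely one, and few such infants would lie more than 2 SD above term on FA. That stands: the space measure carries more of the problem, because a 25% cut-off is crossed far more often than a 2 SD one. It also stands that the bullet, read as two-sided, does score low FA. But nothing says whether bullet or table governs, and the bullet points to a Table 3 while the definitions sit in Table 2.

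The space part depends on two readings: that extra cranial space is the extra-axial space of Figure 5, and that bottom means low rather than worst. Both are plausible, neither is stated. If worst was meant, the protocol needs the same edit.

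Finally, this is a pilot, continuous measures are to be compared by t-test or Mann-Whitney test, and the developmental primary is untouched. Those comparisons keep their sign. They do not repair a primary outcome defined by classification. Nor is this a detail left to a later analysis plan: the protocol states a direction, and it conflicts with its own pilot.

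**Conclusion.** The definition is wrong as written. From the documents alone, bullet and Table 2 disagree on the diffusion rule, and both count high FA as injury against the protocol's own reading. On the two assumed meanings above, the metrics rule has the same fault for extra-axial space.

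The main consequence is dilution. At correlation 0.3, the fall in the composite shrinks from 25.4 to 6.6 points with unimpaired controls, from 17.5 to 9.4 with controls 0.5 SD worse, and from 7.5 to 6.0 with controls 1 SD worse. Cancellation or reversal is possible only in some settings. The sizes rest on assumed normality, baseline, benefit and correlation; the direction of the fault for FA does not.

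**What to change.** State the adverse tail separately for each measure, in the same words in the bullet and in Table 2, consistent with Figures 4 and 5:

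- FA: more than 2 SD below term.
- ADC: more than 2 SD above term.
- Diameter, volumes and surface morphology: lowest 25%.
- Extra-axial space: highest 25%. The same tail should apply to interhemispheric distance, ventricular size and CSF volume if they are scored. The last two appear in the MRI Evaluation table but not in Table 2, so the protocol should say whether they count.

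Use one name for the space measure, one anisotropy index (FA or RA) in the MRI Evaluation table, Outcome measures and General methods, and correct the table number cited in the bullet list. The cost is an edit to one table and a few lines of text, with no added data or visits. It should be made before any infant's outcome is classified.

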Preliminary studies in our laboratory have been undertaken in two phases of a previously approved protocol (IRB #201111063). The first phase was undertaken with healthy pregnancies in their last three weeks of pregnancy taking 8oz of pomegranate juice to ensure that it crossed the placenta. In this study, we confirmed placental transfer of polyphenols with HPLC detectable maternal and cord blood levels rising after two weeks on pomegranate juice. In addition, placenta from 4 women who received pomegranate juice in their last 2 weeks of pregnancy demonstrated decreased expression of heat shock proteins (HSP) in the pomegranate group as compared to controls. For phase II of this study (IRB #201111063) we randomized 41 mothers who were pregnant with infants with a diagnosis of IUGR by fetal ultrasound to receive 8oz pomegranate juice or 8oz apple juice. We were able to undertake MRI scans in 30 infants due to problems with preterm birth or movement on the MRI. On this analysis, the infants born to pregnant mothers who drink 8 oz of pomegranate juice daily in the last trimester of pregnancy demonstrated improved diffusion measures in the brain of their newborn infant representing more mature white matter microstructure and improved brain growth (see figures 1-6 below). Of importance, none of the mothers in the IUGR study had placental examination to determine the possible mechanism of benefit of pomegranate juice in pregnancies complicated by IUGR. This current study will fill this important gap in our knowledge.

[figure not shown]
Figure 1: Pilot data in IUGR Trial in 41 mothers randomized to receive pomegranate or apple juice

[figure not shown]

[figure not shown]
Figure 2: Placental pathology with expression for Heat Shock Protein (HSP 90) in women following labor who received 8 oz of promegranate juice compared to control in women without IUGR.

Figure 3: Cord blood levels of polyphenols at the time of birth in women in the randomized trial who received pomegranate juice (pink) or apple juice (yellow). Note the marked elevation in the levels of two polyphenols in the cord blood of infants whose mothers received pomegranate juice.

[figure not shown]

[figure not shown]

[figure not shown]

[figure not shown]

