**Study plan:**

Dating will be by ultrasound or reliable clinical dating by ACOG standards (33). A dedicated study coordinator will evaluate volunteers to enroll from pregnant patients at the Washington University Medical Center (WUMC) in St. Louis, MO. The Institutional Review Boards of WUMC will approve this study before initiation. A total of eighty consenting women will be randomized to one of two arms POM juice vs POM juice placebo in a 1:1 ratio. The Women’s Health Center at WUMC includes a State-approved collaborative practice of Washington University attending physicians, nurse practitioners, and residents that serve all patients regardless of payer status. The WUMC Center for Advanced Medicine offers a second site for recruitment where university affiliated private practices are located. We anticipate 1-2 patients enrolled per week.

***Treatment group****:* Expecting mothers in this group will be randomized to start a daily regimen of 8 oz glass of pomegranate juice (POM Wonderful). They will keep a daily diary documenting their compliance. They will continue this daily intake up until delivery of their infant.

***Placebo group:***These women will start a daily regimen of an 8 oz of pomegranate free juice placebo that matches taste, calories, and appearance to regular pomegranate juice but lacks polyphenols that contains the same substances without polyphenols. They will also keep a diary of daily intake to help ensure compliance similar to the treatment group. They too will continue to take the placebos up until the time they deliver.

***Both groups:*** All women will be followed up (called) on a weekly basis to assess compliance. Upon delivery, cord blood will be collected and sent for ellagic acid, a polyphenic component. All placental material will be sent for formal pathological exam in addition to the specialized studies outlined below.

Placental Evaluation:

**Overview**: We will test the hypothesis that the active agents in pomegranate extract modulate the villous structure of the placenta, reduces the effects of exogenous stimuli, or both, in the human placenta of women diagnosed to have intrauterine growth restriction.

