**Randomization:**

Mothers will be randomized at the time of enrollment by blinded envelope to either one of the treatment group or a placebo group in a 1:1 ratio.

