**Outcome measures:**

1. **Placenta**

a) Morphometry – weight and size of the placenta.

b) Micrography - number of terminal villi, vasculature and collagen content.

c) Immuno- histochemistry – proliferation, apoptosis and differentiation.

d) Enzyme immunoassays - Heat shock protein 90, Lipid hydroperoxide, Nitrotyrosine assay Paraoxonase 1 expression and Superoxide dismutases

e) RNA and protein analyses of placental tissues - RNA for gene microarray analyses

1. **Pregnancy Outcomes**
   1. Complications of pregnancy – extent of pre-eclampsia, preterm labor
   2. Gestation at delivery
   3. Need for resuscitation at delivery
   4. Cord gas characteristics at delivery
2. **Brain injury and development at term by MR Imaging (see table 2) based on:**
   1. Qualitative MRI injury- white matter injury (WMI) and gray matter injury (GMI)
   2. Brain Metrics on MR imaging
   3. Diffusion- apparent diffusion coefficient (ADC) and fractional anisotropy (FA)
   4. Spectroscopy- lactate and NAA levels in the basal ganglia
   5. Advanced MRI development indices – brain volumes, surface based morphology (SBM, folding indices)
3. **Neurobehavior at term equivalent and neurodevelopmental outcome at 18-24 months** MDI and PDI by Bayley Scale of Infant Development (BSID III) (> 2SD from the norm, score ≤ 70)

***Table 1.*** Summary of the study and procedures for infants recruited into the study

| **Age** |  | **Pregnancy** | **Birth** | **38-41 weeks CGA** | **Discharge** | **18-24 months** |
| --- | --- | --- | --- | --- | --- | --- |
| Maternal data |  | X | X |  |  |  |
| Clinical data |  |  | X | X | X | X |
| Ellagic acid |  |  | X |  |  |  |
| MRI imaging |  |  |  | X |  |  |
| Neurodevelopmental  Behavioral measures | Neurologic/  Sensory |  |  | Dubowitz | Hearing |  |
|  | Attention |  |  | HNNE  attention |  |  |
|  | Global cognition |  |  |  |  | BSID-III  Cognitive |
|  | Motor |  |  |  |  | BSID-III  Motor, Neuro |
|  | Language |  |  |  |  | BSID-III  Language |

* HNNE- Hammersmith Neonatal Neurological Examination Optimality Score

* MRS- MR Spectroscopy; SBM- Surface-based morphology

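### White- and gray-matter injury is scored for extent, but the only comparison the protocol names for it is moderate-or-severe injury yes/no, an event it rates as unlikely; a comparison of the full grades should be stated

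*Protocol*

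**What the plan says.** **What is collected.** Under MRI Evaluation in the Study plan, the first analysis listed is "Systematic qualitative scoring of the nature and extent of brain injury". The measures table there names a white-matter lesion score and, for gray matter, "Cortical and DNGM injury score". The number of grades is not given. The Outcome measures section lists qualitative white- and gray-matter injury as an MRI outcome item of its own and refers the reader to Table 2.

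**How it is used.** In Biostatistical Analyses, General methods, an infant counts as brain-injured on this item by "Moderate to severe injury by qualitative scoring of WMI or GMI". Table 2 repeats the moderate-severe cut and rates the likelihood of injury for the qualitative technique as *Low*. The test-selection paragraph then reads "Categorical variables (such as moderate or severe white matter injury) will be compared using either a chi-squared", and the sentence continues with Kruskal-Wallis as the nonparametric alternative. The same paragraph gives nonparametric continuous variables a Mann-Whitney test.

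**Size.** "A total of eighty consenting women will be randomized to one of two arms POM juice vs POM juice placebo in a 1:1 ratio". On scan yield in the earlier randomized phase with 41 mothers: "We were able to undertake MRI scans in 30 infants due to problems with preterm birth or movement on the MRI". The protocol calls the present study a pilot for a larger trial and states no power, event rate or effect size.

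**The concern.** A score with ordered grades carries more information than one cut through it, and most of that information is lost when the cut sits at a rare event. Here the protocol collects the extent of injury, places the cut at moderate-severe, and expects few infants above it. An infant whose injury moves from mild to none does not change the yes/no result at all.

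The stake is the usefulness of this MRI item for planning the larger trial. A handful of moderate-severe cases in two arms says little about either the presence or the size of an effect. The distribution of grades by arm, from the same scans, says more.

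**Working it through.** The protocol gives no power or event-rate figure for this comparison, so there is none to reproduce.

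**Inputs from the protocol.** 80 women, 1:1, so 40 per arm. Earlier scan yield 30/41 = 73%; 40 × 30/41 = 29.3, so about 29 scans per arm if that yield carries over.

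**Assumptions, not in the protocol.** Two-sided 5% level; four grades (none/mild/moderate/severe); one common odds ratio across all cut-points; control frequencies as stated below.

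**1. What the yes/no comparison needs.** For k events against 0 with n per arm, the uncorrected chi-squared statistic is 2n·k/(2n − k).
- n = 40, k = 3: 80 × 3/77 = 3.12, below the critical value 3.84.
- n = 40, k = 4: 80 × 4/76 = 4.21, p = 0.040.
- Fisher's exact test, n = 40: 5-0 gives p = 0.055, so 6-0 is needed.
- At n = 29 the minimum splits are again 4-0 and 6-0.

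This step needs no assumed effect.

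**2. The best case for the cut.** Suppose treatment abolished moderate-severe injury. Chi-squared power is then the chance of at least 4 control events.

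| Control risk (assumed) | Expected control events, n = 40 | Power, n = 40 | Power, n = 29 |
|---|---|---|---|
| 5% | 2 | 14% | 5% |
| 10% | 4 | 58% | 33% |
| 20% | 8 | 97% | 86% |

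So the weakness depends on *Low* meaning about 10% or less.

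**3. Does Kruskal-Wallis rescue it?** On a two-level variable in two arms, the tie-corrected Kruskal-Wallis statistic is (N − 1)/N times Pearson's chi-squared, here 79/80 of it. Applied to the cut it recovers nothing. Applied to the grades it is the Mann-Whitney test.

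**4. What the grades would add.** With common odds ratio OR, the treated odds at each cut-point equal OR times the control odds. For control 50/40/7/3% and OR 0.35:
- any injury: odds 0.50/0.50 × 0.35 = 0.35, so risk 0.35/1.35 = 25.9%;
- moderate-severe: odds 0.10/0.90 × 0.35 = 0.0389, so risk 0.0389/1.0389 = 3.7%.

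Per 40 infants, the cut compares 4 with 1.5 expected events. The none-versus-any boundary compares 20 with 10.4.

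Power, tie-corrected rank test on the grades (simulated) against chi-squared on the cut:

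| Control none/mild/moderate/severe (%) | OR | n per arm | Rank | Chi-squared | Gain (points) |
|---|---|---|---|---|---|
| 50/40/7/3 | 0.35 | 40 | 61-64% | 21% | about 40 |
| 50/40/7/3 | 0.35 | 29 | 48-49% | 13-14% | about 35 |
| 70/20/7/3 | 0.5 | 29 | 21% | 10% | about 11 |
| 80/10/7/3 | 0.35 | 40 | 34% | 21% | about 13 |
| 80/10/7/3 | 0.5 | 29 | 15% | 9.5% | about 6 |
| 88/5/5/2 | 0.5 | 40 | 14% | 9.5% | about 4 |
| 75/5/15/5 | 0.5 | 40 | 22% | 20% | about 2 |

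Ranges in a cell are results of separate simulation runs. The rank test led in every row, and its rejection rate under no effect was close to 5%. The gain depends mainly on how common mild injury is.

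**The case against.** **The text does not say the scores are tested only at the cut.** This is right. Moderate or severe white-matter injury appears as a parenthetical example, the same sentence names Kruskal-Wallis, and a numeric lesion score could fall under the Mann-Whitney rule for continuous variables. A reader might infer that a graded analysis is ruled out; the protocol does not say that. What stands is narrower: the one variable named for this outcome is already cut to two levels, and no sentence applies either rank test to the grades.

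**The cut belongs to the composite.** Also right as far as it goes. The brain-injury outcome is met by any of several components, and each needs a yes/no definition. But Outcome measures lists qualitative injury separately, and the test paragraph carries the same cut over to the comparison between arms.

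**This could be left to the analysis plan.** Silence could. Here the protocol itself names a variable and a test, so the wording is open to criticism.

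**The size of the loss rests on assumptions that favour the rank test.** Largely right. A reader might conclude that the cut loses most of the power. That is so in scenarios with frequent mild injury and rare moderate-severe injury, but not generally: at 75/5/15/5% the difference is about 2 points. A common odds ratio across all grades is also the condition that suits the rank test.

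**The fix does not make the comparison powerful, and the trial does not depend on it.** True. At 29 per arm the most favourable row above still has under 50% power. This is a pilot that claims none, and Table 2 rates diffusion, metrics, volumes and surface measures as high likelihood. The point concerns this one comparison and not the trial as a whole.

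**Conclusion.** The point holds in a limited form. The protocol collects graded white- and gray-matter injury scores, names only a moderate-severe yes/no comparison for them, and rates the likelihood of such injury as low. At 40 per arm, or about 29 scanned, that comparison cannot reach significance against zero events with fewer than 4 events by chi-squared or 6 by Fisher. The full-grade rank test did better in every scenario examined, by about 2-13 points of power where mild injury is uncommon and up to about 40 where it is common.

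Those gains rest on assumed four-grade frequencies, a common odds ratio of 0.35 to 0.5 and a two-sided 5% level, none of which the protocol states. The 29 per arm rests on the earlier scan yield carrying over. The direction of the conclusion is firm under proportional odds; its size is not known.

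**What to change.** In Biostatistical Analyses, General methods, state that the white-matter lesion score and the cortical/deep nuclear gray-matter injury score will each be compared between arms on their full ordered scale by the Mann-Whitney test. With two arms this is equivalent to the Kruskal-Wallis test already named. Give a proportional-odds common odds ratio with its 95% confidence interval as the effect estimate, and report the proportion with moderate-severe injury by arm descriptively. The moderate-severe cut may stay as a component of the composite brain-injury definition.

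The cost is a few sentences. Extent of injury is already scored, so no further scans, readings or participants are needed. The downside is small: a common odds ratio is less familiar to clinicians than a risk difference and rests on a proportional-odds assumption. The descriptive proportions keep the familiar figure in view.
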